#### 4.11.6 Dose-Limiting Toxicity

The following summaries will be generated based on the DLT analysis set by dose level and overall:

- A summary of the number and proportion of patients who experience a DLT during the DLT evaluation period.
- A summary of the number and proportion of TEAEs experienced by patients during the DLT evaluation period.

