### **9.1. SAFETY ANALYSES**

All safety analyses will be performed on the Safety Analysis Set. Interim safety data will be examined on an ongoing basis to ensure patient safety and to comply with the clinical study Dose Escalation rules.

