| 
 
To assess safety and tolerability of agenT-797 infusion
 
                                                                                                    | 
 
Number and severity of adverse events (AEs) and dose-limiting toxicities (DLTs) at evaluated dose levels
 
                                                                                                                                                                                                                                                                                                                                                                                                                                                                                                                                                                                                                                                                                  | 
 
Frequency of AEs and affected patients at evaluated dose levels
 
                                                                                                                                                                                                                                                                                                                                                                                                                                                                                                                                                                                                                        |

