### 4.5 Analysis Sets

Three subject analysis sets are defined for the study analyses, as follows:

- **The All Subject Analysis Set** will include all patients who have completed informed consent, irrespective of the study treatment administered. This analysis set will be used for the disposition summary and the listing of study populations.
- **The Safety Analysis Set** will include all patients who received agenT-797. This analysis dataset will be used for safety analysis and all listings other than listings of subject disposition and study populations.
- **The Dose-Limiting Toxicity Analysis Set** will include all patients who either experienced a DLT within 28-day observation or completed study treatment and 28-

day observation for DLT without experiencing DLT. The DLT analysis set will be used for the analysis of DLT rates and for determining MTD.

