### **4.11.3 Safety Evaluation**

The DLT analysis set will be used for the DLT rate and MTD of agentT-797. The safety analysis set will be used for all other safety analyses.

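### SAP 4.11.6 puts the DLT-period TEAE summary on the DLT analysis set, which drops treated patients who die in the window without a DLT, and gives a proportion with no denominator

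*Combined protocol and SAP*

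**What the plan says.** SAP 4.11.6 introduces its two summaries with one statement of population: "The following summaries will be generated based on the DLT analysis set by dose level and overall". The first is patient-based: "A summary of the number and proportion of patients who experience a DLT during the DLT evaluation period". The second is "A summary of the number and proportion of TEAEs experienced by patients during the DLT evaluation period".

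Three other places bear on the population:

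- SAP 4.11.3 gives the DLT set a narrow use, "The DLT analysis set will be used for the DLT rate and MTD of agentT-797", and continues: "The safety analysis set will be used for all other safety analyses". SAP 4.5 gives the DLT set the same two uses.
- Protocol 9.1 states: "All safety analyses will be performed on the Safety Analysis Set".
- SAP 4.5 defines the DLT set to "include all patients who either experienced a DLT within 28-day observation or completed study treatment" and the 28-day observation without a DLT. The safety set is everyone who received agenT-797.

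On the unit, SAP Table 2 gives the primary estimator as "Frequency of AEs and affected patients at evaluated dose levels", and the AE summaries in SAP 4.11.4 report the number and percentage of patients.

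**The concern.** A TEAE summary is neither a DLT rate nor an MTD determination. SAP 4.11.6 and SAP 4.11.3 therefore name different populations for the same table, and a programmer cannot follow both.

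The difference is not neutral. Membership of the DLT set depends on what happens after infusion, and one way to fail to complete observation is to die. In moderate to severe ARDS early deaths are foreseeable: the plan makes 30-day mortality an endpoint, and its stopping criteria exempt 30-day deaths attributed to the primary disease. A table restricted to patients who had a DLT or completed observation is selected on survival, and the patients it leaves out may be those with the worst events.

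This is the only AE summary that the SAP restricts to the DLT evaluation period, and AEs by dose level are the primary endpoint. The missing denominator adds a second uncertainty: the reader cannot tell what a percentage in the table is a percentage of.

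**Working it through.** The plan gives no figure to reproduce here. The check applies the membership rule to each kind of patient, then gives a small illustration.

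**1. Population named for the DLT-period TEAE summary**

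| Source | Population |
|---|---|
| SAP 4.11.6 | DLT analysis set |
| SAP 4.11.3 | Safety set (the DLT set is for DLT rate and MTD) |
| SAP 4.5 | Safety set for safety analysis (same limited use of the DLT set) |
| Protocol 9.1 | Safety Analysis Set |

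**2. Who is in the table.** Protocol 8.1.4 requires a DLT to be at least possibly related to treatment.

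| Treated patient | Had a DLT? | Completed observation? | In DLT set | In safety set |
|---|---|---|---|---|
| Completes the window, no DLT | no | yes | yes | yes |
| Dies in the window of an at least possibly related event | yes (Grade 5) | no | yes | yes |
| Has a non-fatal DLT, then dies in the window of an unrelated event | yes | no | yes | yes |
| Dies in the window of an unrelated event, no DLT | no | no | **no** | yes |

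Only the last row is lost, but that patient is lost with every TEAE, not just the fatal one.

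**3. Window.** SAP 4.11.6 does not define its evaluation period. SAP 3.6 and protocol 8.1.4 use 14 days; the DLT set in SAP 4.5 uses 28. If the table covers 14 days and membership needs 28, a patient without a DLT who dies on Days 15 to 28 also loses all TEAEs from Days 1 to 14. With equal windows the last row of the table above is still lost.

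**4. Unit.** The first bullet of SAP 4.11.6 and the summaries in SAP 4.11.4 count patients. The second bullet takes a proportion of TEAEs and names no denominator.

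**5. Illustration.** Assumptions: a cohort of 15 (the maximum for Cohort 4); a given share of treated patients die in the window of a TEAE without any DLT; no one else has a fatal event in the window; everyone else qualifies for the DLT set. The documents give no such rate, so 10% to 40% is shown, with counts rounded to whole patients. The chance that at least one patient is removed is 1 − (1 − share)^15.

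| Assumed share | Fatal TEAE, safety set | Fatal TEAE, DLT set | Chance at least one patient is removed |
|---|---|---|---|
| 10% | 2/15 (13.3%) | 0/13 | 1 − 0.9^15 = 0.79 |
| 20% | 3/15 (20.0%) | 0/12 | 1 − 0.8^15 = 0.96 |
| 40% | 6/15 (40.0%) | 0/9 | 1 − 0.6^15 > 0.99 |

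Wilson limits, the interval named in SAP 4.2, with z = 1.96: [p + z²/(2n) ± z√(p(1−p)/n + z²/(4n²))] / (1 + z²/n).

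- 3/15: (0.2 + 0.128 ± 1.96 × √(0.01067 + 0.00427)) / 1.256 = (0.328 ± 0.2395) / 1.256, which gives 7.0% to 45.2%.
- 0/12: lower limit 0; upper limit z²/(n + z²) = 3.84/15.84 = 24.2%.

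In a cohort of 6, one such death gives 1/6 (16.7%) on the safety set and 0/5 on the DLT set.

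**The case against.** The strongest reply is that little is lost overall. The by-subject AE listing in SAP 4.11.4 is presented by dose level with onset date, severity, outcome and causality, and SAP 4.5 puts such listings on the safety set. SAP 4.11.5 adds summaries and listings of deaths and serious TEAEs, and SAP 4.11.2.4 gives 30-day all-cause mortality with a score interval, though it does not say by dose. A reader might infer that early events by dose cannot be recovered. That goes too far: with cohorts this small they can be counted by hand from the listing. What stands is that no summary table shows them.

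A reader might also infer that fatal events not judged DLTs are zero by construction. SAP 4.11.6 plans no row by grade or fatality, and a patient with an earlier DLT who later dies of another cause stays in. The exclusion applies to patients with no DLT at all.

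Two provisions limit the affected group. Protocol 8.1.1 says anticipated deterioration of the disease is not an AE, so some ARDS deaths are TEAEs in neither set. SAP 3.9 treats patients withdrawn after infusion as evaluable for DLT, which competes with SAP 4.5, but it does not address death.

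On the unit, one could read the proportion as in-window TEAEs over all TEAEs, and so as a measure of timing. The SAP does not say this; loose wording for patients with TEAEs is at least as likely, given the parallel first bullet. Event counts are themselves legitimate under SAP Table 2.

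Finally, protocol 9.1 taken literally would bar the DLT set even for the DLT rate, so the argument rests mainly on SAP 4.11.3 and 4.5.

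**Conclusion.** The point holds for one table. SAP 4.11.6 contradicts SAP 4.11.3 and the use stated in SAP 4.5, and following it removes treated patients who die in the window without a DLT, together with all their TEAEs. That is selection on survival. The missing denominator is a separate, smaller defect.

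The size depends on how many such deaths occur, which the documents do not say. The contrast of 20.0% with zero rests on an assumed 3 deaths in 15, each a TEAE and none in a patient with a DLT. It describes patients with a fatal event, a row the SAP does not itself plan, and shows direction and possible scale only.

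A reader might infer that dose decisions were distorted. The documents do not support that: Part 1 is marked completed, the SMC weighs all the safety data, including toxicities outside the DLT period, and no passage makes this table an input to escalation. The consequence is for how early safety by dose is reported. The correction is worth making because it is cheap and removes a contradiction.

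**What to change.** In SAP 4.11.6, keep the DLT analysis set for the proportion of patients with a DLT. Replace the second bullet with:

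> On the safety analysis set, number and percentage of patients with at least one TEAE with onset during the DLT evaluation period, by worst grade, and number of events, by dose level and overall. Patients who die or leave early remain in the denominator.

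Using the safety set also means this table does not depend on settling SAP 3.9 against SAP 4.5 on evaluability.

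The new bullet cannot be programmed until its period is fixed. The 14-day passages (SAP 3.6, protocol 8.1.4) and the 28-day passage (SAP 4.5) must be reconciled, and the resulting period stated in SAP 4.11.6.

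The cost is a change of SAP wording and one table shell, with no new data. Early event rates may look less favourable than under the present text.

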#### 4.11.7 Clinical Laboratory Evaluation

All lab parameters listed will be collected and analyzed at the time points detailed in the schedule of assessments in Appendix 1.

The following laboratory assessments will be analyzed:

- Hematology: hemoglobin, hematocrit, platelet count, red blood cell count, white blood cell count, mean corpuscular volume, mean corpuscular hemoglobin, absolute neutrophils count, absolute lymphocytes count, absolute monocytes count, absolute eosinophils count, absolute basophils count, absolute bands count, percentage of neutrophils, percentage of lymphocytes, percentage of monocytes, percentage of eosinophils, percentage of basophils and percentage of bands.
- Coagulation: prothrombin time, activated partial thromboplastin time and international normalized ratio.
- Clinical chemistry: albumin, alkaline phosphatase, alanine aminotransferase, aspartate aminotransferase, blood urea nitrogen, urea, calcium, carbon dioxide, chloride, C-reactive protein, creatinine, creatinine clearance, ferritin, glucose, lactate dehydrogenase, magnesium, phosphorus, potassium, sodium, total bilirubin, direct bilirubin, indirect bilirubin and total protein.
- Urinalysis: pH, ketones, specific gravity, bilirubin, protein, blood, glucose.
- Human herpes virus 6 and 7 tests.
- Human immunodeficiency virus 1 and 2, hepatitis B and C, and human T-lymphotropic virus serologies, hepatitis B virus DNA and hepatitis C virus RNA.
- Pregnancy tests.
- Circulating cytokines.

The following summaries will be generated:

- A summary of each laboratory parameter by time point.
- A summary of the change from baseline in each laboratory parameter by time point.
- A summary of the number and percentage of patients experiencing abnormal values, by laboratory parameter and time point.
- A summary of the number and percentage of patients experiencing low, normal or high values at baseline and at selected post-baseline time points, by laboratory parameter (shift table).

- A summary of the number and percentage of patients experiencing treatment-emergent laboratory abnormalities, by laboratory parameter.
- A summary of the number and percentage of patients experiencing treatment-emergent clinically significant laboratory abnormalities, by laboratory parameter.

The observed values and change from baseline of the safety laboratory assessments will be summarized using descriptive statistics showing the number of observations (n), mean, median, SD, minimum, and maximum value. Categorical results will be summarized based on the number and percentage in each category, presented by time point.

Laboratory results outside the normal range will be flagged. The abnormal values will be flagged with 'L' (low) for values below the lower limit of the laboratory's normal range or 'H' (high) for values above the upper limit of the laboratory's normal range. Abnormal values will be graded as not clinically significant (NCS) or clinically significant (CS). Clinically significant laboratory values will be recorded by the investigator as AEs.

A by-subject listing of all laboratory data will be provided with abnormal values highlighted.

#### **4.11.8 Vital Signs, Physical Findings and Other Observations Related to Safety**

Physical examination, vital signs, and electrocardiogram (ECG) will be collected at the time points detailed in the schedules of assessments in Appendix 1.

##### **4.11.8.1 Physical examination**

A complete physical examination will be performed at screening and will include assessment of height (during screening only) and weight and vital signs, examination of head, eyes, ears, nose, throat, neck, cardiovascular, chest/lungs, abdomen (including liver and spleen size), extremities, neurological, skin, and lymph nodes, as well as a brief neurologic examination.

Clinically significant physical exam findings will be summarized and listed.

##### **4.11.8.2 Vital signs**

Vital signs include body temperature, heart rate, respiratory rate, systolic and diastolic blood pressure. Vital signs are measured by the physician or the nurse and are part of the complete physical examination until Day 29 and measured each time it is clinically indicated.

A summary of each vital sign parameter and its change from baseline will be generated.

A by-subject listing will be provided with the reference ranges.

##### **4.11.8.3 ECG**

A single, 12-lead ECG will be performed. The ECG will be evaluated by the Investigator as 'Normal', 'Abnormal, NCS' or 'Abnormal, CS'.

A summary of each ECG parameter will be generated.

A by-subject listing will be provided.

## 6 Appendix

### APPENDIX 1

**Table 4. Schedule of Assessments**

| Assessment                                                         | Screening      | Treatment Period             |   |   |   |   |        |                     |                     |                     |                        | EOH a | 30-Day F/U |
|--------------------------------------------------------------------|----------------|------------------------------|---|---|---|---|--------|---------------------|---------------------|---------------------|------------------------|------------------|------------|
| Study Day                                                          | ± 4            | 1                            | 2 | 4 | 6 | 7 | 10 ± 1 | 14 ± 1 b | 21 ± 2 b | 28 ± 2 b | 32 to EOH b | Day of discharge | 30 ± 2     |
| Informed consent                                                   | X c |                              |   |   |   |   |        |                     |                     |                     |                        |                  |            |
| Inclusion/exclusion                                                | X c |                              |   |   |   |   |        |                     |                     |                     |                        |                  |            |
| HLA serotype                                                       | X c |                              |   |   |   |   |        |                     |                     |                     |                        |                  |            |
| Medical history & demographics                                     | X c |                              |   |   |   |   |        |                     |                     |                     |                        |                  |            |
| Physical examination d                                  | X c | Daily monitoring/assessments |   |   |   |   |        |                     |                     |                     |                        | X                | X          |
| Vital signs e                                           | X c | Daily monitoring/assessments |   |   |   |   |        |                     |                     |                     |                        | X                | X          |
| ECG f                                                   | X c | X                            |   |   |   |   |        |                     |                     | X                   |                        | X                | X          |
| Radiological evaluation (X-ray/CT)                                 | X c | X                            |   |   |   |   |        |                     |                     |                     |                        | X                |            |
| Concomitant medications & procedures                               | X              | Continuously collected       |   |   |   |   |        |                     |                     |                     |                        |                  |            |
| Adverse events g                                        | X              | Continuously collected       |   |   |   |   |        |                     |                     |                     |                        |                  |            |
| Hematology h                                            | X c | Daily monitoring/assessments |   |   |   |   |        |                     |                     |                     |                        | X                | X          |
| Coagulation h                                           | X c | X                            |   | X |   | X | X      | X                   | X                   | X                   |                        | X                | X          |
| Clinical chemistry h                                    | X c | Daily monitoring/assessments |   |   |   |   |        |                     |                     |                     |                        | X                | X          |
| Urinalysis i                                            | X c | X                            |   | X |   | X | X      | X                   | X                   | X                   |                        | X                | X          |
| Pregnancy test (WOCBP) j                                | X              |                              |   |   |   |   |        |                     |                     |                     |                        |                  |            |
| Serum for cytokine analyses k                           | X c | X                            |   | X |   | X | X      | X                   | X                   | X                   |                        | X                |            |
| Whole blood for persistence of agentT-797 (peripheral persistence) | X c | X l               | X | X | X | X | X      | X                   | X                   | X                   |                        | X                | X          |
| Whole blood for cfDNA (tissue persistence)                         | X c | X m               | X | X | X | X | X      | X                   | X                   | X                   |                        | X                | X          |
| Bronchoalveolar lavage (iNKT cell                                  | X c | X                            |   | X |   | X | X      | X                   | X                   | X                   |                        | X                |            |

| Assessment                                                                            | Screening      | Treatment Period                       |   |   |   |   |        |                     |                     |                     |                        | EOH a | 30-Day F/U |
|---------------------------------------------------------------------------------------|----------------|----------------------------------------|---|---|---|---|--------|---------------------|---------------------|---------------------|------------------------|------------------|------------|
| Study Day                                                                             | ± 4            | 1                                      | 2 | 4 | 6 | 7 | 10 ± 1 | 14 ± 1 b | 21 ± 2 b | 28 ± 2 b | 32 to EOH b | Day of discharge | 30 ± 2     |
| presence and biomarker) k,n                                                |                |                                        |   |   |   |   |        |                     |                     |                     |                        |                  |            |
| Epithelial sampling by bronchial protected specimen brush (RNA analysis) o | X c | X                                      |   | X |   | X | X      | X                   | X                   | X                   |                        | X                |            |
| Serum for alloantibodies                                                              |                | X c                         |   |   |   |   |        | X                   |                     |                     |                        | X                |            |
| agenT-797 cell infusion                                                               |                | X                                      |   |   |   |   |        |                     |                     |                     |                        |                  |            |
| Arterial blood gas                                                                    | X              | Daily monitoring/assessments as needed |   |   |   |   |        |                     |                     |                     |                        | X                | X          |
| Symptoms of ARDS p evaluation (Berlin definition) q             | X              | Daily monitoring/assessments as needed |   |   |   |   |        |                     |                     |                     |                        | X                | X          |
| SOFA score r                                                               | X              | Daily monitoring/assessments as needed |   |   |   |   |        |                     |                     |                     |                        | X                |            |
| Viral burden assessment (swab), or endotracheal suction as feasible (RT-PCR)          | X s | X                                      | X | X | X | X | X      | X                   | X                   | X                   |                        | X                |            |
| Viral shedding assessment as feasible                                                 |                | X                                      |   |   |   |   |        |                     |                     |                     |                        | X                |            |
| D-dimer, CPK, cardiac troponins, and ferritin                                         |                | Every 12h, as feasible                 |   |   |   |   |        |                     |                     |                     |                        | X                |            |

Abbreviations: AE: adverse events; AESI: adverse events of special interest; ARDS: acute respiratory distress syndrome; d: day(s); cfDNA: cell free DNA; CPK: creatine phosphokinase; CT: computed tomography; ECG: electrocardiogram; EOH: End-of-Hospitalization; F/U: Follow-up; HLA: human leukocyte antigen; h: hour (s); IL: interleukin; iNKT cells: invariant natural killer T cells; RT-PCR: reverse transcriptase polymerase chain reaction; SAE: serious adverse event; SOFA: sequential organ failure assessment; WOCBP: women of childbearing potential.

a End-of-Hospitalization is defined as patient discharge from hospital and/or death. If a patient is discharged at Day 30, 30-day Follow-up will be the same as EOH. After discharge, a patient will enter Safety Follow-up period and the patient will be contacted by telephone 3 and 6 months after discharge regarding any SAEs and to confirm survival, as feasible..

b In case of earlier discharge from the hospital, no visit is expected until 30-Day Follow-up.

c Performed before infusion of agenT-797 on D1. These samples will be obtained at the time of the routine labs blood draws.

d A complete examination, as feasible, will be performed at Screening and symptom-directed and medically indicated physical examinations are done thereafter.

e Vital signs include body temperature, heart rate, respiratory rate, systolic and diastolic blood pressure and are assessed by physician or nurse. On the day of infusion of agenT-797 (D1), measurements will be 15 min prior to infusion, and 15 min, 30 min, 1h, 2h, 3h, and 4h postinfusion.

- f ECG to be performed at Screening, Day 1 predose and EOH, 30-Day Follow-up, and at other times as clinically indicated.
- g Only AEs associated with study procedures and/or leading to withdrawal and all SAEs will be collected prior to study drug infusion. Patients are monitored for toxicities following infusion. All other AEs, SAEs, and AESIs will be collected in the Safety Follow-up period.
- h Hematology/coagulation/clinical chemistry: Complete blood count with automated and/or manual differential will be collected daily, as feasible. Coagulation: activated partial thromboplastin time and international normalized ratio. Clinical chemistry: includes but not limited to albumin, alkaline phosphatase, alanine aminotransferase, aspartate aminotransferase, blood urea nitrogen, urea, calcium, chloride, C-reactive protein, creatinine, glucose, lactate dehydrogenase, magnesium, phosphate/phosphorus, potassium, sodium, total bilirubin, direct and indirect bilirubin, total protein, and beta-2-microglobulin and will be collected daily, as feasible. All will be collected at EOH and at 30-Day Follow-up.
- i Urinalysis: pH, ketones, specific gravity, bilirubin, protein, blood, and glucose. Will be done at the days indicated and at EOH and at 30-Day Follow-up.
- j Pregnancy testing for women of child-bearing potential: serum test at Screening.
- k Cytokines/biomarkers: D1 – preinfusion, end of infusion, and at 2, 4, and 8 hours postinfusion agenT-797, and as feasible thereafter. Cytokines for analysis may include but are not limited to: epidermal growth factor, eotaxin, fibroblast growth factor-basic, granulocyte-colony stimulating factor, granulocyte-macrophage colony stimulating factor, hepatocyte growth factor, interferon-alpha, interferon-gamma, IL-1 beta, IL-1 alpha, IL-1RA, IL-2, IL-2R, IL-3, IL-4, IL-5, IL-6, IL-7, IL-8, IL-9, IL-10, IL-12 (p40/p70) IL-13, IL-15, IL-17A, IL-17F, IL-22, IP-10, monocyte chemoattractant protein-1, MIG, MIP-1 alpha, MIP-1 beta, Regulated upon Activation, Normal T Cell Expressed and Presumably Secreted, tumor necrosis factor-alpha, vascular endothelial growth factor, and matrix metalloproteinase-9.
- l To be obtained 5, 15, and 30 min, and 1, 2, and 4 hours postinfusion.
- m To be obtained 2 hours postinfusion.
- n To be obtained in intubated patients if clinically indicated using microlavage techniques when possible.
- o To be obtained in intubated patients when possible.
- p Evaluations including physical examination and procedures required for lung injury score evaluation (chest X-ray, PaO2/FiO2 ratio, positive end-expiratory pressure, compliance, mL/cm H2O) as needed, including daily or more often until recovery ([ARDS 2012](#)).
- q As needed.
- r SOFA score will be calculated using results of the following tests: PaO2, FiO2, platelet count, need for mechanical ventilation, Glasgow Coma score, bilirubin, mean arterial pressure or use of vasoactive medications, creatinine, and diagnosis of COVID-19 ([SOFA](#)).
- s Patients must be SARS-CoV-2 or influenza positive at diagnosis; refer to [Section 4.7.1 of the study protocol](#)
